### **4.3. Description of the interventions**

#### **4.3.1.Initial training of the senior physicians**

All the senior physicians will have been administered, in advance in this study, identical training as to the complete procedure of pediatric IO access (theoretical and practical course using task-trainer). Theoretical and practical evaluations using an assessment scale established by the Simulation Laboratory (Oriot on 2012) for the University Course of Pediatric Emergency Procedures (Simulation Laboratory, Faculty of Medicine of Poitiers, [name]; (Diplôme Universitaire des Gestes d'Urgence en Pédiatrie (Laboratoire de Simulation, Faculté de Médecine de Poitiers, [name]).

#### **4.3.2.Mannequin and scenarios**

We shall use a high-fidelity mannequin, SimNewB\* (Laerdal\*), available in the Simulation Laboratory of Poitiers, along with our bank of scenarios simulating shock in an infant (every scenario will be drawn by lots among the cases remaining). These scenarios will oblige teams to manage a simulated infant shock, within a highest level of priority, requiring insertion of an IO access. We shall use nine scenarios of infant shock, drawn by lots, among 18 available: Hypovolemic shock (3rd digestive sector, acute dehydration due to gastroenteritis, extensive burns, diabetic ketoacidosis, diabetes insipidus, post-traumatic cerebral salt wasting, adrenal failure due to congenital adrenal hyperplasia), hemorrhagic shock (subgaleal [subaponeurotic] hematoma, fulminating hemoptysis due to pulmonary artery hypertension, severe trauma with retro-peritoneal hemorrhage, severe trauma with peritoneal and femoral hemorrhage), medication or food-induced anaphylactic shock, cardiogenic shock (viral myocardopathy, supra-ventricular tachycardia), septic shock (purpura fulminans), shock due to hemolytic anemia (malaria with acute hemolysis), and cardio-respiratory arrest complicating a decompensated state of shock due to a tamponade.

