#### 4.3.7. Simulation session repetition

The frequency of repeated simulation sessions will be one of the varying parameters, and will define distribution into one of two randomized groups, necessary for providing answers to secondary objectives. Repetition will take place either every 6 weeks i.e. 9 / year (group 1), or every 6 months i.e. 3 / year (group 2).

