##### 4.5.1.2. Drawing lots for random distribution of each team into one of the 2 of simulation session programs

Once the teams have been constituted, drawing lots will be performed according to a list that will be previously established by the study's methodologist, so as to distribute the 12 teams in 2 groups of 6 teams :

**Group 1** will be constituted by 6 teams of 4 persons each, and each of these teams will undergo simulation sessions once every **6 weeks**, for a total of 9 sessions in 12 months.

**Group 2** will be constituted by 6 teams of 4 persons each, and each of these teams will undergo simulation sessions once every **6 months**, for a total of 3 sessions in 12 months.

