##### **9.1.4.Comparison of the variation in performance scores between groups 1 and 2 = Evaluation of the effect of repeated simulation on performance**

To study variation in performance (global performance, IO access and teamwork evaluation scores) between the time point of inclusion (T0) and the simulation program's endpoint, the relative variation of various scores will be calculated  $\{([final\ score] - [score\ T0]) / (score\ T0)\}$ . These relative variations will be compared between the 2 groups using a Student's t-test. An ANOVA test will be used to search for a possible effect due to participant status.

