**4. Local anesthesia**

|                                              |   |
|----------------------------------------------|---|
| Absence of anesthesia (in conscious patient) | 0 |
| Local anesthesia                             | 1 |

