| TOTAL over 40                                             |                                                                                                                                                                                                                                                                                                                                                                                    |   |                                                                                                                                                                                                                                                                        |   |                                                                                                                                                                                                                                                                                                                                                    |
| TOTAL over 100                                            |                                                                                                                                                                                                                                                                                                                                                                                    |   |                                                                                                                                                                                                                                                                        |   |                                                                                                                                                                                                                                                                                                                                                    |

**CTS - Clinical Teamwork Scale™ (Global)**Please note: **Not relevant-** The task was not applicable to the scenario.

| Overall                                                        | Not Relevant             | Unacceptable | Poor |   |   | Average |   |   | Good |   |   | Perfect |

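### Scenarios are drawn by lot with no stated unit of draw and no balance between groups, so the six-versus-six comparison of first and last sessions carries avoidable noise or, on one reading, confounding

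*Protocol*

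**What the plan says.** Section 4.3.2 describes a bank that ranges from dehydration to cardio-respiratory arrest with tamponade: "We shall use nine scenarios of infant shock, drawn by lots, among 18 available". The rule for assigning them is that "every scenario will be drawn by lots among the cases remaining". The unit of the draw is not given, and no section balances, stratifies or matches scenarios between groups or fixes the first or last one.

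Section 4.5.1.2 has the methodologist prepare a list in advance "so as to distribute the 12 teams in 2 groups of 6 teams". Section 4.3.7 sets the sessions at "either every 6 weeks i.e. 9 / year (group 1), or every 6 months i.e. 3 / year (group 2".

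Section 9.1.4 defines the performance endpoint as the change from T0 to the final score divided by the T0 score, and "These relative variations will be compared between the 2 groups using a Student's t-test". Section 9.1.3 tests changes across sessions within each group by repeated-measures ANOVA. It mentions a mixed model as a possibility and names no scenario factor.

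The protocol itself ties its measurements to the scenario. Section 4.3.3 attributes the stress to the scenarios and has parents enter only where the scenario provides for it. Item 4 of the IOPAS scores zero for "Absence of anesthesia (in conscious patient". The Clinical Teamwork Scale form has a box for cases where "The task was not applicable to the scenario".

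**The concern.** The endpoint in section 9.1.4 uses two sessions per team, so two drawn scenarios determine both the change and its denominator. If scenarios differ in difficulty, part of the difference between groups reflects which cases were drawn. Six teams per group average out little of this.

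At stake is the answer to the repetition question, a secondary objective and the only one that the randomisation serves. Depending on how the draw is made, a real effect may be missed or a scenario difference may be taken for a training effect. A model fitted later can adjust for scenario only where the design has let scenario vary separately from group and session.

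**Working it through.** **No plan figure to reproduce.** Section 9.2 sizes the trial for a correlation and leaves the power for secondary questions to be computed afterwards. The checks below therefore measure consequences only.

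**Inputs**
- Six teams per group (4.5.1.2); two sessions enter the endpoint (9.1.4); two-sided 5% level (9.3 gives p < 0.05; taken as two-sided).
- For scale only: a 2.1-point difference and an SD of 1.02 on the 20-point IO scale, quoted in 9.2 from previous studies.
- Assumed, because not given: the share f of within-team, within-session score variance due to scenario, from 0.1 to 0.5.
- Simplification: absolute change. The planned ratio also puts the T0 scenario into the denominator.

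**Reading 1: each team has its own draw.** Write the total within-team variance per session as 1. A team's change has variance 2, of which 2f is scenario. The t-test estimates its standard error from these same changes, so its level stays at 5% (simulated 4.9% to 5.2%). The cost is precision. Assume a correlation of 0.5 between T0 and final scores, so that the SD of the change without scenario effects is 1.02. With a scenario SD of k × 1.02, the SD of the change is 1.02 × √(1 + 2k²) and f = 2k²/(1 + 2k²).

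| k | f | SD of chance imbalance between groups, √(4/6) × k × 1.02 | simulated power for 2.1 points |
|---|---|---|---|
| 0 | 0 | 0 | 89% |
| 0.25 | 0.11 | 0.21 | 86% |
| 0.5 | 0.33 | 0.41 (formula 0.42) | 75% |
| 1 | 0.67 | 0.83 | 47% |
| 1.5 | 0.82 | 1.25 | 29% |

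**Reading 2: all teams of a group share the draw.** The scenario part no longer averages over teams. The group difference has variance 2 × 2(1 − f)/6 + 2 × 2f, but the t-test sees only the first term. The ratio is 1 + 6f/(1 − f), and type I error is P(|t₁₀| > 2.228/√ratio).

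| f | ratio | 2.228/√ratio | type I error |
|---|---|---|---|
| 0.1 | 1.67 | 1.73 | 12% |
| 0.2 | 2.50 | 1.41 | 19% |
| 0.3 | 3.57 | 1.18 | 27% |
| 0.5 | 7.00 | 0.84 | 42% |

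Simulation agrees (11.5%, 18.9%, 26.8%, 41.9%).

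**Reading 3: one draw serves all teams.** If both groups share the first and the last scenario, scenario cancels from the group comparison. Each session in 9.1.3 then has one scenario, so a session effect cannot be told from a scenario effect. The cancellation needs the last scenario to be common: Group 2's last session is its third and Group 1's is its ninth. If the last scenario is shared only within a group, the comparison falls under a milder form of reading 2.

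**What matching first and last scenarios across groups buys.** The true variance of the group difference falls from 2 × 2/6 to 2 × 2(1 − f)/6, so the true standard error falls by 1 − √(1 − f): 5%, 11%, 16% and 29% for f = 0.1, 0.2, 0.3 and 0.5. The analysis determines how much of this is realised.
- *Unpaired t-test:* its estimated standard error still contains the scenario variance. Type I error is 4.1% at f = 0.1, falling to 1.2% at f = 0.5. At an effect where the free draw has 80% power, power becomes 81% to 86%.
- *Paired t-test:* degrees of freedom drop from 10 to 5 and the critical value rises from 2.228 to 2.571. The interval width relative to the free draw is (2.571/2.228) × √(1 − f) = 1.09, 1.03, 0.97 and 0.82. Break-even is f = 1 − (2.228/2.571)² ≈ 0.25, so pairing gains only above roughly 0.2 to 0.3.

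**The case against.** Drawing scenarios at random is a legitimate choice, and with an independent draw per team it introduces no bias. That stands. A reader might infer that the free draw by itself inflates false positives; the protocol does not support this, because inflation needs a draw shared within a group, which section 4.3.2 neither states nor excludes. Nor may a reader add the harms together: lost precision, confounding with group and confounding with session follow from alternative readings. Nine scenarios for nine Group 1 sessions makes a common draw a natural reading, and if its first and last scenarios are common the group comparison is clean.

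The evidence on size is thin. The between-scenario variance is unknown. One IOPAS point is close to the quoted SD of 1.02, but that is the largest shift one item can give. Every scenario requires IO access, and the other 19 of the 20 points carry no scenario condition. The not-relevant box is the teamwork scale's own way of handling inapplicable tasks and does not prove biased scores. This is why the figures are ranges under assumption.

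A scenario term could also be left to an analysis plan, and the mixed model in 9.1.3 could use all sessions. This stands for the analysis. The draw is a design matter: no model separates scenario from group or session once the sessions have been run with the two tied together.

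**Conclusion.** The point holds as a cheap design improvement to a secondary comparison. The protocol should state the unit of the draw and balance scenarios between groups. With a draw per team the cost is precision, of unknown size. With a draw shared within a group, type I error is about 12% to 42% for an assumed scenario share of 10% to 50%. With a fully common draw the cost is confined to the session comparison in 9.1.3.

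It would be tempting to promise a 5% to 29% smaller standard error from matching. That is the reduction in the true standard error; an unpaired t-test does not deliver it. Matching still loses no power under the planned test, and it rules out the confounded draw.

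The figures rest on normal scores, absolute rather than relative change and an assumed scenario variance.

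**What to change.** 1. State in section 4.3.2 the unit of the scenario draw.
2. Have the methodologist prepare, together with the allocation list in 4.5.1.2, six scenario orders drawn by lot. Give each order to one team in each group, with the same T0 scenario and the same final scenario within each pair.
3. Vary the position of scenarios across the six Group 1 teams, so that session and scenario can be separated in 9.1.3.
4. Name scenario as a factor in the mixed model of 9.1.3 and use that model for the group comparison in 9.1.4. An unpaired t-test on the matched data remains valid but conservative; a paired t-test gives up 5 degrees of freedom.

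The cost is one more prepared list and less flexibility when a session has to be rescheduled. Scenarios still vary from session to session within a team.

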#### **4.3.3.Stress**

Stress will be that which is connected to the very scenarios (hypoxia, haemodynamic decompensation, onset of convulsions), but also to an environment inducing a stressful atmosphere (monitor beeps and alarms), including the untimely entry of simulating parents into the emergency room, if this latter case has been foreseen in the scenario.

#### **4.3.4.Supervisors and evaluation**

Two independent supervisors at a time will evaluate each simulation session of the Sim-Stress research protocol.

These supervisors, who are members of the University Hospital of Poitiers

(CHU de Poitiers) Simulation Laboratory, will be chosen in random manner. They each have different specialities, and are all simulation trainers, qualified in performing debriefing sessions.

This team of supervisors will consist of [name] (pediatric intensivist), [name] (pediatric emergency physician), [name] (surgical intensivist), [name] (adult emergency physician), and 4 emergency or pediatric fellows. They will analyze global performance with the respect to algorithm, IO access performance and global teamwork - leadership and communication. The mean between the two supervisors' scores will be used as the reference value. Interobserver reproducibility will be calculated according to the scale used.

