#### **4.3.5.Video**

All the simulation sessions will be videotaped, so as to be viewed for analysis of actions and interventions performed during the simulation scenario (evaluation of the global competence and strategies used to manage the induced stress). Furthermore, videos will also further be viewed for analysis by two other independent observers, who will not know the team members. The mean between the two supervisor scores will be used as the reference value. Interobserver reproducibility of the teamwork scale (leadership and communication) will be calculated. Stress

University Hospital of Poitiers - CHU de Poitiers Sim-Stress management strategies implemented by the senior physician will also re-evaluated. A comparison will be performed with the supervisors observing the live simulation sessions.

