#### 4.3.6. Debriefing

All the simulation sessions will be followed by a debriefing session, according to Rudolph's method of "*good judgment*" (Rudolph 2006, Rudolph 2008), and led by supervisors previously trained in this technique (University course Training at the University of Paris Descartes).

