#### **4.5.3.Methods of assessment using objective evaluation scales**

All the assessments using objective evaluation will be made by two observers, independent of each other, and in single manner, as far as their affectation to both groups and management of scenarios is concerned. Calculation of intra-class correlation coefficients will be performed for each of the scales used evaluation, even if such scales may have already been validated, so as to measure inter-observer reproducibility.

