### **7.3. Methods and schedule for collection, quantification and analysis of performance and stress evaluation parameters**

#### **7.3.1. Performance quantification**

Performance quantification will be based upon objective evaluations obtained using a number of evaluation scales (global team performance, IO access, leadership, and teamwork), as conducted by two independent supervisors, direct observers of each simulation session.

Subsequent video recording visualisation by the same two, direct observers, will allow for evaluation of stress management strategies implemented by the team leader.

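### Section 4.5.3 appears to promise that raters are masked to group, but the reference performance score comes from live in-house supervisors, and the protocol does not say how they stay unaware of group

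*Protocol*

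**What the plan says.** All places are in the protocol.

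- **Masking.** Section 4.5.3, among the measures against bias, has two observers score the objective scales "in single manner, as far as their affectation to both groups and management of scenarios is concerned". The word blind does not appear, but masking to group is the likeliest meaning.
- **Who scores.** Section 4.3.4 assigns two supervisors to each session, chosen at random from a team of eight (four specialists and four fellows) belonging to the hospital's own simulation laboratory. They "are all simulation trainers, qualified in performing debriefing sessions". For the reference score it says: "The mean between the two supervisors' scores will be used as the reference value". Section 7.3.1 likewise bases performance on two supervisors who observe each session directly.
- **Who debriefs.** Section 4.3.6 has every session followed by a debriefing "led by supervisors previously trained in this technique".
- **Who views the video.** Section 4.3.5 says "videos will also further be viewed for analysis by two other independent observers, who will not know the team members". It then states a reference value again, as the mean of two supervisor scores. Section 7.3.1 assigns review of the leader's stress-management strategies differently: "Subsequent video recording visualisation by the same two, direct observers". Section 4.2.2 gives that review to the supervisors.
- **What the scores feed.** Section 9.1.4 compares the relative change from T0 to the final score between the groups by t-test. Group 1 has nine sessions, one every 6 weeks; Group 2 has three, one every 6 months (Section 4.5.1.2).

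**The concern.** Masking to group is listed as a protection, but the protocol contains no mechanism for it. Live raters from one small laboratory see the teams in person, and the groups differ in how often they attend. A rater who recognises a team from several recent sessions can guess its schedule and expect it to have improved.

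The BAT and CTS rest on graded judgement, and the TAPAS is an in-house scale whose validation is unfinished (Section 4.2.1), so expectation could move these scores. At T0 neither arm has been trained in the study. At the end the rater may know which team has had more practice. A bias of that kind falls on the final score, and so on the contrast in Section 9.1.4. Averaging two raters who share the expectation does not remove it. The intra-class correlation in Section 4.5.3 does not reveal it either, because shared expectation raises agreement.

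The outside video observers in Section 4.3.5 could supply a better-protected score, but the text leaves unclear whether their scores are ever the reference.

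**Working it through.** **Session count.** Section 4.4.2.2 gives 6 × 9 = 54 and 6 × 3 = 18, total 72. This reproduces. With two raters per session and eight supervisors, each scores 72 × 2 / 8 = 18 sessions on average.

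**Familiarity at the final session.** Inputs: pool of 8 and 2 raters per session (Section 4.3.4); k earlier sessions, 8 in Group 1 and 2 in Group 2. Assumption: a fresh draw each session, with every pair equally likely.

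- A given final-session rater has already scored the team: 1 − (6/8)^k.
- At least one of the two has done so: 1 − (C(6,2)/C(8,2))^k = 1 − (15/28)^k.
- Mean number of earlier ratings of that team by a given rater: k × 2/8.

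| | Group 1 (k = 8) | Group 2 (k = 2) |
|---|---|---|
| Given rater has scored the team before | 0.90 | 0.44 |
| At least one of the two has | 0.99 | 0.71 |
| Mean earlier ratings by a given rater | 2.0 | 0.5 |

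The random draw does not equalise familiarity. The difference comes from the schedule itself.

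**What a bias would do to the test.** The protocol gives no size for rater bias, so a range is assumed. Let b be a shift favouring one group, in units of the between-team SD of the analysed quantity (the relative change in Section 9.1.4). With 6 teams per group, two-sided 5% and df = 10, the critical value is 2.228 and the non-centrality is b × √(6/2) = 1.732b. The rejection probability when there is no true effect is:

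| b (assumed) | False-positive rate |
|---|---|
| 0 | 5.0% |
| 0.25 | 6.8% |
| 0.5 | 12.3% |
| 0.75 | 21.8% |
| 1.0 | 34.7% |

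**Which score is the reference.** For performance, Sections 4.3.4 and 7.3.1 agree on the live supervisors. Section 4.3.5 introduces the outside observers and then gives its own reference-value sentence. That sentence either repeats the rule for the live pair or, loosely worded, means the video pair; the text does not settle it. For stress-management strategies the conflict is open: Section 4.3.5 has outside observers view the recordings and the leader's strategies re-evaluated, Section 7.3.1 names the same two live observers, and Section 4.2.2 names the supervisors. Sections 9.1.3 and 9.1.4 do not say whose scores they use.

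**The case against.** The strongest reply is that safeguards exist and the reach is limited. Raters are drawn at random, every scale is scored twice with agreement reported, and outside video observers are already planned, with a comparison against the live supervisors. Randomisation serves secondary objectives only (Section 4.3.7). The primary outcome consists of cortisol, Holter, blood pressure and self-report measures, which these raters do not score. All of this is correct, and it limits the point to the secondary comparison. It does not supply masking.

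A reader might also infer more than the text supports:

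- **That each rater sees a Group 1 team nine times and so knows its group and session number.** The pool sees it nine times. One supervisor is expected to score a Group 1 team 9 × 2/8 = 2.25 times and a Group 2 team 3 × 2/8 = 0.75 times. Familiarity differs by arm; knowledge of group is a plausible consequence, not a stated fact.
- **That the scorers coach the teams they score.** Section 4.3.6 draws the debriefers from the supervisors but does not say they are the two who scored that session.
- **That the protocol flatly contradicts itself on the performance score.** The explicit conflict over the video concerns stress-management strategies. For performance, Section 4.3.5 is ambiguous.
- **That the bias can be put in IOPAS points from the SD of 1.02 in Section 9.2.** That is the SD of a raw score from a previous study, whereas Section 9.1.4 tests relative change. The IOPAS is also largely a checklist of observable actions, so it is less open to expectation than the BAT or CTS.

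Finally, video scoring is no cure if done carelessly. Not knowing the team members is not the same as being masked to group, and one pair viewing all 72 recordings would see nine tapes of some teams and three of others. That objection stands, and the fix has to meet it.

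**Conclusion.** The point holds as a design weakness in a secondary, randomised comparison. Section 4.5.3 appears to list masking to group as a protection, but the reference score comes from live in-house raters for whom no masking is described. Under the protocol's own rater scheme their prior familiarity with a team at the final session is 0.90 against 0.44. These figures assume a fresh random draw of two from eight at each session.

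Whether scores would in fact be biased, and by how much, cannot be read from the protocol. The 7% to 35% range is conditional on an assumed shift of 0.25 to 1.0 between-team SD of the analysed score, and shows only that a comparison of six teams with six is sensitive to such a shift. Reading Section 4.5.3 as a masking statement is an inference from garbled text. If no masking was intended, the absence of protection remains and the section needs rewording. The primary outcome is untouched.

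**What to change.** 1. For the group comparison in Section 9.1.4, make the mean of the two outside video observers of Section 4.3.5 the reference for TAPAS, BAT and CTS, and for the IOPAS items visible on video.
2. Have them score the first and final recordings of all 12 teams first: 12 × 2 = 24 recordings, two per team in both groups, so that the number of tapes does not reveal group. Present these in random order with group, date and session number removed, before any intermediate recording is viewed.
3. Keep the live scores for the within-group session analyses in Section 9.1.3, inter-observer agreement, a sensitivity analysis of 9.1.4, and IOPAS items the recording does not show. Puncture site and insertion angle, which Appendix 5 has observed after insertion, may be among these.
4. Reconcile Sections 4.2.2, 4.3.4, 4.3.5, 4.5.3 and 7.3.1 on who views the video and whose mean is the reference. State in 4.5.3 exactly who is masked to what, and how.

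Cost: some extra scoring per recording and a shuffled viewing list. Every session is already filmed and the observers are already planned, so no new staff, sessions or participants are needed. The between-group and within-group analyses would then rest on different raters, which the report should state.
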